### Design of the FitSpirit approach

FitSpirit partners with schools to provide activities that get young girls moving and keep them physically active over the long term. It offers tools and services within a holistic approach based on flexible, individualized support to help schools engage girls through girl-only activities tailored to their challenges and their preferences. Non-competitive group activities are planned, organized and led by a member of the school staff, the school program leader, with the support from a regional coordinator. The physical and health education teacher, or any other school employee, can become the FitSpirit school leader. FitSpirit activities can run during the entire school year, with most schools organizing activities only between February and May and for a minimum of 8 weeks (unpublished data). For example, only 67 of the 285 partner schools registered in the school year 2018–2019 have organized FitSpirit activities during fall. In addition, during this same school year, an average of 19 activities have been organized by the partner schools.

FitSpirit offers its support through several services, but mainly the ones listed below. Each partner school decides the extent to which they use and exploit these every year and this information is collected by FitSprit in order to conduct a process evaluation.

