Between 2017 and 2019, a stratified random sampling method was applied to recruit girls for research. Each school leader randomly selected five to ten research participants among all girls who provided consent, irrespective of grade. The FitSpirit organization sent the invitation to research participants via email and their school leader could help them have access to the online questionnaires at school.By the year 2019–2020, the FitSpirit organization moved towards the invitation of all girls with consent to participate in the research project (15,000 potential participants). FitSpirit send invitations for the research via email and the school leaders are no longer involved in research.For the follow-ups, the same girls are contacted again by the FitSpirit organization, whether or not they still participate in FitSpirit in subsequent years, as illustrated in Fig. 2.Research participants will be contacted for follow-ups each year until May 2022.

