FitSpirit appreciation (secondary outcomes)	• Reasons for participation (in-house questionnaire) • Words associated with FitSpirit (in-house questionnaire) • Participation level (in-house questionnaire) • Satisfaction level (in-house questionnaire) • Injuries (in-house questionnaire)

*PA* Physical activity

**Table 2 Tab2:** Questions evaluating physical activity levels

Questions	
• Over a typical or usual week, on how many days are you physically active for a total of at least 60 min in total per day? Consider only the activities that made you breathe harder and sweat at least a little. ○ None (zero days) ○ 1 day ○ 2 or 3 days ○ 4 to 6 days ○ Everyday	
• In the last 7 days, how long did you use active forms of transportation to get around, like walking to school or cycling to get to work, the shopping center or a friend’s place? (Enter hours AND minutes. You can enter 0 h and 0 min if you have not used active modes of transportation.)	
• In the last 7 days, how long did you do physical activity in your leisure time including exercising, playing an organized or non-organized sport or playing with your friends? (Enter hours AND minutes. You can enter 0 h and 0 min if you have not been active during your leisure time.)	

Data are collected at the beginning and at the end of each school year. Study participants are invited via their personal email address provided at registration to complete the online questionnaire. The end of year questionnaire is also sent to study participants who dropped out from FitSpirit. The longitudinal design of the study will allow the research group to perform an assessment over a prolonged period of time. It will also allow for an evaluation of the persistence of the effects of the program over the summer school break.

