### Statistical analyses

The primary research question to be answered relates to the impact of FitSpirit on the participants’ PA level. The secondary research questions relate to the impact of FitSpirit on other lifestyle habits (sedentary activities, eating and sleeping habits), health perception, physical self-efficacy, body satisfaction, and participants’ appreciation of the FitSpirit approach. Both continuous (ex: total minutes of PA/week) and categorical data (ex: meeting or not the recommendation for moderate-to-vigorous PA) will be used as dependent variables, while the number of FitSpirit activities/year and of years of participation at FitSpirit will be used as independent variables. Data will be analysed in a cross-sectional fashion using chi-square test and Fisher’s exact test (depending on the sample size) to evaluate for instance the relationship between categories of PA levels and categories by the number of years of participation in FitSpirit. Pearson’s test will assess, for example, the correlation between the number of days/week meeting PA recommendations and levels of physical self-efficacy. In addition, analyses of variances will compare the levels of PA (total minutes of PA/week) between grade levels. Longitudinal analyses will evaluate primarily the change in PA levels, and in other secondary outcomes afterwards. Statistical adjustments will be performed using, for instance, the variation in the length of intervention from one school to another or the baseline lifestyle habits of participants as covariates.

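### Years of participation pools girls still in FitSpirit with girls who have left, so the PA-by-years table cannot separate current attendance, selective staying and a lasting effect

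*Protocol article*

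**What the plan says.** Statistical analyses names two exposures: "the number of FitSpirit activities/year and of years of participation at FitSpirit will be used as independent variables". It then states "Data will be analysed in a cross-sectional fashion using chi-square test" or Fisher's exact test, and gives as an example "the relationship between categories of PA levels and categories by the number of years of participation in FitSpirit". Current versus former participation is not named as a variable. The same section puts the primary weight on longitudinal change in PA, and mentions baseline lifestyle habits and length of intervention as possible covariates.

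Girls who leave stay in the study. Under Study population, "the same girls are contacted again by the FitSpirit organization, whether or not they still participate in FitSpirit in subsequent years". Under Data collection, "The end of year questionnaire is also sent to study participants who dropped out from FitSpirit".

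Two further facts bear on timing. Design of the FitSpirit approach describes a programme "with most schools organizing activities only between February and May". In Table 2, the two duration items cover the previous week ("In the last 7 days, how long did you do physical activity in your leisure time"), and the days-per-week item asks about a typical week.

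**The concern.** A count of years records how much programme a girl has had, not whether she is in it now. At an end-of-year wave the low counts mix new participants with girls who left one or more years ago, while the highest possible count holds only girls who never left. Three things can then raise PA across the year categories:

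- **Current attendance.** The wave falls during or soon after the usual activity months and the PA items concern a recent or usual week. Sessions can enter a current attender's answer but not a leaver's.
- **Selective staying.** More active girls may be more likely to continue. Study population says that participants have mixed sport backgrounds.
- **A lasting effect**, which is what the study wants to learn about.

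The study has no control group, so contrasts by amount of participation are among its few internal comparators. Former participants are the group that can show whether activity persists after leaving. Under the stated coding they are spread through the lower year categories without a label.

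**Working it through.** The plan gives no figure for this analysis, so there is none to reproduce. The check asks whether the planned table can show a gradient when no lasting effect exists.

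**Inputs from the protocol article.** Base rate 14%, read as the share of girls who meet the PA recommendation (Background). An 8% increase in the cited study of about 3,000 girls (Sample size determination). That increase concerned vigorous PA and is not stated to be absolute or relative, so it serves only as an upper illustrative value in percentage points. Sample sizes of 3,000, and of 15,000, which is the potential pool.

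**Assumptions.** Three equal entry cohorts, surveyed at the end of the third year. Yearly probability of staying s = 0.60. For selective staying, half the girls have a 20% rate and s = 0.75, and half have an 8% rate and s = 0.45 (mean rate 14%). Full response, independent girls, two-sided alpha 0.05.

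**Make-up of the year categories at s = 0.60**

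- 1 year: leavers 0.40 + 0.40, current 1.00. Share current = 1.00/1.80 = 56%; weight = 1.80/3 = 0.60.
- 2 years: leavers 0.60 × 0.40 = 0.24, current 0.60. Share current = 0.60/0.84 = 71%; weight = 0.84/3 = 0.28.
- 3 years: current 0.60² = 0.36. Share current = 100%; weight = 0.36/3 = 0.12.

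**Case (a): 8 points for current attenders, no lasting effect.** 14 + 8 × 0.556 = 18.4%; 14 + 8 × 0.714 = 19.7%; 14 + 8 × 1 = 22.0%.

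**Case (c): selective staying only.** Share of the more active type at 1 year = 1.50/(1.50 + 2.10) = 0.417, so PA = 8 + 12 × 0.417 = 13.0%. At 2 years the share is 0.9375/(0.9375 + 0.6975) = 0.573, giving 14.9%. At 3 years it is 0.5625/(0.5625 + 0.2025) = 0.735, giving 16.8%.

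**Chance that the chi-square test rejects.** Noncentrality = N × Σ w(p − p̄)² / [p̄(1 − p̄)], with 2 degrees of freedom. In case (a), p̄ = 0.1923 and the sum is 0.0001357. At N = 15,000 the noncentrality is 15,000 × 0.0001357/0.1553 = 13.1, and the rejection probability is 0.910.

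| Case | 1, 2, 3 years (%) | N = 3,000 | N = 15,000 |
|---|---|---|---|
| (a) current-only, 8 points | 18.4, 19.7, 22.0 | 0.285 | 0.910 |
| (b) current-only, 4 points | 16.2, 16.9, 18.0 | 0.109 | 0.385 |
| (c) selective staying only | 13.0, 14.9, 16.8 | 0.465 | 0.993 |
| (d) selective staying plus 4 points | 15.2, 17.8, 20.8 | 0.732 | 1.000 |
| (e) true lasting effect, 3 points per year | 17.0, 20.0, 23.0 | 0.758 | 1.000 |

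Cases (a) to (d) have no lasting effect, yet their gradients are of the same kind as in (e).

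**Effect of splitting by status.** In case (a), current girls are at 22% in every year category, and former girls are at 14% in both categories where they occur, so the gradient disappears. In case (c), current girls still show 14.0%, 15.5% and 16.8%. The split removes the current-attendance part but not the selective-staying part.

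**The case against.** Four points can be made for the plan.

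1. *The table is only an example, and longitudinal change comes first.* This stands and limits the weight of the point. However, years of participation is declared as an independent variable generally, and no status term is stated for the longitudinal analyses either.
2. *The second exposure, activities per year, may already mark status.* If it is counted per girl for the current year, a leaver scores zero, and a model with both exposures could partly separate the groups. The article does not say that it is counted per girl or that the two are modelled together. A two-way test on year categories cannot use it in any case.
3. *Pooling is inferred.* No sentence says that leavers enter the table unlabelled, and years of participation is not defined further. A fuller plan may settle both. As the article stands, the named exposure and test, applied to end-of-year data that include leavers, produce the pooling.
4. *Related limits are disclosed.* The Discussion mentions the missing control group and the possibility that the most motivated girls respond. It does not mention selective continuation in the programme.

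Two stronger readings are tempting, and the documents do not support them. A reader might infer that any association with years reflects attendance and staying rather than a lasting effect. Case (e) shows that a real lasting effect would look the same, so the explanations are confounded and none is excluded. A reader might also turn the average of 19 activities per school into minutes of PA per week and call that the bias. The 19 counts activities that schools organised, not sessions a girl attended. The documents give no session length, individual attendance or dropout rate.

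**Conclusion.** The point holds as a matter of identification. Followed as written, the cross-sectional table gives current and former participants with equal year counts the same exposure value. It therefore cannot separate current attendance, selective staying and a lasting effect. It does not follow that the programme has no lasting effect, or that the planned longitudinal change analysis is invalid.

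The size is not known. The illustrated gradients from 1 to 3 years, 1.8 to 5.6 percentage points with no lasting effect (16.2 to 18.0 in case (b), 15.2 to 20.8 in case (d)), depend on assumed staying rates, type mix and effects. The rejection probabilities also assume full response and independent observations. This is an inexpensive improvement to the analysis, worth making because long-term change is the study's stated purpose.

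**What to change.** At each wave, derive programme status (current or former, with time since leaving) alongside years completed. Then:

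- Report the PA-by-years table separately for current and former participants.
- Include status as a time-varying term, with baseline PA as a covariate, in the longitudinal models. State whether activities per year is counted per girl and whether it enters the same model.
- Base any statement on persistence after leaving on former participants' PA compared with their own earlier waves.
- State that a gradient across years among current girls may still reflect selective staying.

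The cost is one derived variable, some analysis wording and smaller strata. FitSpirit must already know who has left in order to follow them up, so a status flag could accompany the anonymous data that it transfers. No new data collection should be needed.

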**Methods:**

The study is conducted among schools that partner with FitSpirit every year. It started in 2018 and will be completed in 2022. The intervention comprises motivational talks, a turnkey running program, PA sessions and special events. Study participants fill out an online questionnaire twice a year. Follow-up questionnaires are sent at the end of each school year to the study participants who dropout from FitSpirit. The main outcome, changes in PA levels, is evaluated using questions validated for adolescents. Secondary outcomes are health (perceived health); lifestyle habits (sedentary activities, eating and sleeping habits); psychosocial outcomes (physical self-efficacy and body satisfaction); and FitSpirit appreciation (activity participation and satisfaction). Most questions originate from questionnaires validated for the adolescent population. Cross-sectional and longitudinal analyses will be performed.

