Evidence to date highlights the need for additional longitudinal studies, with a large sample size, conducted in real-life settings to draw clearer conclusions on the effects of school-based PA interventions specifically tailored to adolescent girls. Real life studies inform on the effectiveness of interventions implemented in routine circumstances [28]. FitSpirit is a non-for-profit organization that has been offering school-based, girl-only PA program in Canada since 2007. Their intervention is promising due to the non-competitive and mobilization approaches but remained understudied. In 2017–2018, over 12,000 girls participated regularly in FitSpirit activities delivered in 250 partner schools. Through their activities and event offerings, FitSpirit aims to get adolescent girls moving, and keep them physically active over the long term. The objective of this article is to describe the protocol used to evaluate the changes resulting from the implementation of the FitSpirit approach in schools. It presents a longitudinal, quasi-experimental, non-controlled study that aims to evaluate the following outcomes:

Primary outcome: Changes in PA levels among teenage girls who take part in FitSpirit activities in their school.

Secondary outcomes: Health (perceived health); lifestyle habits (sedentary activities, eating and sleeping habits); and psychosocial determinants (physical self-efficacy and body satisfaction) associated with the FitSpirit program. The study also aims to evaluate the girls’ level of participation as well as their appreciation towards some aspects of the FitSpirit approach.

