### Trial status

This article presents the protocol as last approved on May 15, 2019. The recruitment began on February 2018 and will be completed at the end of 2022.

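### Girls with earlier FitSpirit years have no pre-programme measurement, so an overall change in physical activity mixes two quantities and adjustment for baseline habits can remove part of the years-of-participation effect

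*Protocol article*

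**What the plan says.** The Background states that the organisation "has been offering school-based, girl-only PA program in Canada since 2007" and that in 2017–2018 "over 12,000 girls participated regularly in FitSpirit activities delivered in 250 partner schools". Under Trial status, "The recruitment began on February 2018".

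The Study population section sets no condition on earlier participation. For 2017–2019, "Each school leader randomly selected five to ten research participants among all girls who provided consent, irrespective of grade". From 2019–2020 every consenting girl is invited, about 15,000 potential participants.

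Questionnaires are completed at the start and end of each school year (Data collection). Most schools run activities only from February to May (Design of the FitSpirit approach).

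In Statistical analyses, "the number of FitSpirit activities/year and of years of participation at FitSpirit will be used as independent variables". The longitudinal analysis concerns primarily the change in PA, with no stated reference point. Baseline appears once in that section, as an example of adjustment: "the baseline lifestyle habits of participants as covariates".

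**The concern.** The study has no control group, so the question about the programme's impact rests mainly on change within girls. That change needs a reference point with one meaning. For a girl new to FitSpirit, a questionnaire completed before her school's first activity is a pre-programme measurement. For a girl with earlier FitSpirit years it is not, and data collection began too late to supply one.

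The article itself accepts that effects may carry over. The programme aims at lasting activity, and the Data collection section says the design will show whether effects survive the summer break. A start-of-year value in a returning girl is thus partly a possible result of the programme. Two things are at stake: what an overall change in PA means, and whether adjustment for baseline habits is safe when years of participation is the exposure. The limitations in the Discussion cover the missing control group, self-report, participation bias and school selection, but not earlier exposure.

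**Working it through.** The plan has no figure to reproduce here. The 15,000 is a count of potential participants, and no effect size, error rate or returning share is stated.

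**1. Can girls enter already exposed?** The programme started in 2007 and recruitment in 2018, a gap of 11 years. Inputs: 250 schools, 5 to 10 girls selected per school, over 12,000 regular participants in 2017–2018. Assume one round of selection in that year, with every school taking part:
- 250 × 5 = 1,250, and 1,250/12,000 = 10.4%
- 250 × 10 = 2,500, and 2,500/12,000 = 20.8%

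On that assumption at least 79% of that year's regular participants were not selected in the round. Any of them still active and consenting in 2019–2020 would be invited then, with an earlier FitSpirit year behind them. How many that is, the article does not say.

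**2. What does a within-year change measure?** In 2018–2019, 67 of 285 schools ran fall activities: 67/285 = 23.5%. In the other 218/285 = 76.5%, a start-of-year questionnaire precedes that year's activities, for new and returning girls alike. The start-to-end change therefore usually spans one activity season for both. What differs is the starting level: unexposed for new girls, after one or more earlier seasons for returning girls.

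**3. What does mixing do to an overall change?** Let D be the change in new girls, p the share of girls returning, and r the returning girls' change relative to D. Then

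overall change = D × [(1 − p) + p × r]

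All three are assumptions. D = 8 points is used only as a scale; the figure 8% is what the article cites from an outside study of vigorous PA.

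| p | r = 0 | r = 0.5 | r = 1 | r = 1.25 |
|---|---|---|---|---|
| 0.25 | 6.0 | 7.0 | 8.0 | 8.5 |
| 0.50 | 4.0 | 6.0 | 8.0 | 9.0 |
| 0.75 | 2.0 | 5.0 | 8.0 | 9.5 |

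Example: 8 × [0.5 + 0.5 × 0.5] = 6.0. The overall change is smaller than D only if r is below 1, equals it at r = 1, and exceeds it above 1.

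**4. What does the adjustment do?** Let K be FitSpirit years before the first questionnaire, and suppose habits at that questionnaire are H = a + bK and later PA is c + dK + eH. The total effect of K is d + eb. A model that adjusts for H estimates d and drops eb. For a girl with K = 0, H precedes exposure and adjustment is harmless. The terms b, d and e are unknown, so the part removed cannot be sized.

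**5. Is this a power problem?** Illustration: two-sided 5% test, 14% at the start (the Background figure for girls, taken as the proportion meeting the recommendation, although its wording is ambiguous), time points treated as independent, no clustering or non-response. With 15,000 per time point, power is about 1.00 for 8 points, 1.00 for 4 and 0.998 for 2. With 3,000 it is 1.00, 0.99 and 0.58. At the full potential sample the issue is the meaning of the estimate, not power.

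**The case against.** The strongest reply is that the article never says it pools new and returning girls, and never calls the first questionnaire the baseline. It names years of participation as an independent variable, which can separate the two groups, and a fuller analysis plan may define the reference point. This largely stands. A reader might infer that pooling against the first questionnaire is planned, but the text only leaves it open. What does not fall away is the consequence of the entry rule and the start date. No model term turns a returning girl's first value into a pre-programme one, and the adjustment for baseline habits is named without a limit to unexposed girls.

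A reader might also infer that the effect is diluted, to 80% or 40% of its size if 20% or 60% of girls are returning. That takes r = 0, meaning no further change in returning girls. The documents do not support this, and girls who stayed may be those who respond well, which would push the overall figure up. Assuming evenly spread ages and years can produce a returning share, but nothing in the article backs such a spread. The statement "The study is conducted among schools that partner with FitSpirit every year" does not show how many schools or girls return.

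Nor is a returning girl's change a comparison entirely within exposure. In about three quarters of schools it brackets that year's activities.

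Last, the stated aim covers all girls who take part, and the Sample size section includes them all deliberately for representativeness. Replacing the primary set with new entrants only would change the question. That objection stands, and the fix below respects it.

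**Conclusion.** The point holds in a limited form. Girls with FitSpirit years before their first questionnaire can enter and have no pre-programme measurement. An overall change in PA therefore combines change from an unexposed level with re-exposure change that may carry earlier effects. Adjusting the years-of-participation effect for habits measured after exposure began can remove part of that effect.

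The direction and size of any bias are unknown. With D = 8 points and p from 0.25 to 0.75, the overall change runs from 2.0 to 9.5 points for r between 0 and 1.25; all of these inputs are assumed. Dilution is one possibility among several. With a sample near 15,000 the practical risk is a precise estimate of a quantity without one clear meaning.

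**What to change.** In Statistical analyses:

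- Define baseline relative to first FitSpirit participation.
- Report the longitudinal change in PA separately for girls with no earlier FitSpirit year whose first questionnaire precedes their school's first activity, and for returning girls by number of earlier years.
- Interpret only the first group's change as change from a pre-programme level. Keep the all-participant estimate beside it, so that the real-life question is still answered.
- Do not adjust the years-of-participation effect for habits measured after exposure began. Adjustment for habits recorded before first exposure can stay.

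This needs wording and a stratified report, using a variable the plan already requires. The cost is a smaller set and a wider interval for the new-entrant estimate. Girls in schools with fall activities may drop out of that set if their first questionnaire came too late.
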